### Sample size calculation

Since no effects are analysed for the implementation outcomes, no sample size calculation is was made. The case number planning of the key informants and healthcare providers is determined by the project structure. The sampling of the key informants and healthcare providers is limited by the number of the seven cooperating CCCs and the associated 49 remote centres. All key informants will be included into the quantitative survey (phase 1/2: *n* = 7, phase 3: *n* = 56). Interviews will be conducted with CCCs key informants (*n* = 7) in all phases and in phase 3 with additional 14 key informants of the remote cancer centres. Purposeful sampling will be used for selection.

In phases 2 and 3, 105 healthcare providers will be recruited for the questionnaire survey in the CCCs. It will be assumed that each CCC (*n* = 7) has at least 15 healthcare providers involved into the care structures. In phase 3, healthcare providers in remote cancer centres will also be included in the survey. Based on the assumption that each CCC will reach additional seven remote cancer centres in phase 3 with five healthcare providers available for survey, a further 245 healthcare providers will be surveyed (total in phase 3: *n* = 350).

Purposeful sampling is used to conduct in-depth interviews with at least 18 healthcare providers in all phases.

For the qualitative interviews of patients, at least five patients at all CCCs and at least ten patients at remote cancer centres are recruited by purposeful sampling until saturation is reached. Sampling is informed by sex, age, tumour entity, exercise therapy, and experiences with the MOVE-ONKO care pathway as reported in patient questionnaires which are part of the evaluation of intervention outcomes.

#### Data analysis

Quantitative data are analysed using IBM SPSS 27 (or newer). Questionnaire scales are summarised according to the respective test manual guidelines. Variables are described as frequencies (categorical variables) or mean with standard deviation (metric variables). Differences between observations in the primary outcome (physical functioning) are analysed using a linear model with the value of physical functioning at t2 as dependent variable and its value at t0 as independent variable and adjusting for the cluster structure of the data (different centres) and patient characteristics (age, gender, education). Missing values will be replaced by multiple imputation. An additional sensitivity analysis will only use complete cases. Estimated parameters, *p* values and confidence intervals are reported. *P* values smaller than 0.05 will be considered statistically significant.

Other quantitative outcomes are analysed using the same analysis scheme as for the primary outcome.

The audio recordings of all individual interviews will be transcribed and pseudonymised. The transcripts will be analysed using the MAXQDA Analytics Pro software, following the structuring qualitative content analysis method by Kuckartz [41]. Two researchers will independently code and finally analysed by consensus. Main categories will be developed based on the interview guideline, and inductive subcategories will be developed during the coding process.

The results of the quantitative and qualitative surveys are finally brought together in evaluation workshops (triangulation).

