### Study design

The prospective observational mixed-methods study (without control arm) will combine perspectives of key informants, healthcare providers and patients based on survey data and in-depth semi-structured interviews.

The study comprises three phases (Fig. 3): 1) preparation, 2) implementation in seven Comprehensive Cancer Centres (CCCs) in three large regions in Germany, 3) implementation in remote cancer centres.

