### Sample size calculation

The intervention is anticipated to cause a change in the subscale Physical functioning of the EORTC QLQ-C30 during the three-month intervention period between t0 and t2, with an effect size (ES) = 0.3 in repeated measures design. In phase 2, participants will be recruited across seven CCCs, and analyses will be performed across all centres. In phase 3, there will be 49 peripheral centres in addition to the seven CCCs. This brings up the total number of recruitment centres to 56 that will involve patients in the MOVE-ONKO care pathway and its evaluation. The following assumptions are considered: power = 0.80, intra-subject correlation = 0.5, intraclass correlation (ICC) = 0.01 (patients in centres), and drop-out = 10%. To demonstrate an effect of 0.3 between t0 and t2, a total of approximately 280 patients are required from seven centres (*n* = 40 per centre) in phase 2. In phase 3, around 1,960 patients are needed from 56 centres.

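### In this single-arm study the primary model has no time or group term, so no parameter it reports estimates or tests the t0-to-t2 change on which the study is sized.

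*Protocol article*

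**What the plan says.** **Target.** Sample size calculation (intervention outcomes) rests on a "change in the subscale Physical functioning of the EORTC QLQ-C30 during the three-month intervention period between t0 and t2". That change is specified "with an effect size (ES) = 0.3 in repeated measures design". The other inputs are "power = 0.80, intra-subject correlation = 0.5, intraclass correlation (ICC) = 0.01 (patients in centres), and drop-out = 10" per cent. It asks for about 280 patients from seven centres in phase 2 and about 1,960 from 56 centres in phase 3.

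**Design.** Study design opens with "The prospective observational mixed-methods study (without control arm"), and Evaluation of intervention outcomes repeats that there is no control group.

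**Analysis.** Data analysis gives the purpose first: "Differences between observations in the primary outcome (physical functioning) are analysed using a linear model". It then defines this as a "linear model with the value of physical functioning at t2 as dependent variable and its value at t0 as independent variable". The covariates enter by "adjusting for the cluster structure of the data (different centres) and patient characteristics (age, gender, education"). The model's parameters are to be reported with p values and confidence intervals, and significance is set at 0.05. The remaining quantitative outcomes follow the same scheme. The article mentions no time factor, change score, centring or contrast between the t2 and t0 means.

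**The concern.** Regressing a follow-up score on its baseline is the usual analysis of covariance when a group term is added, and that term is then the effect. With one arm there is no such term. What remains is a slope on t0, an intercept, and coefficients for age, gender, education and centre. The study question is whether mean physical functioning moves between t0 and t2, and none of these quantities answers it. If the section is followed literally, the printed output contains no estimate, interval or p value for the quantity that the study was powered to detect. The analyst would have to choose the contrast later, possibly with the data in view.

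**Working it through.** **1. The plan's own figure.** For a paired comparison, the standardised change is dz = 0.3/√(2(1 − 0.5)) = 0.3. At 80% power and two-sided 5% this needs 90 patients. The design effect is 1 + (40 − 1) × 0.01 = 1.39, and 90 × 1.39/0.9 = 139. The stated 280 is not reproduced. The nearest route is the per-group size of a two-sample comparison, 176 × 1.39/0.9 = 272. That discrepancy is separate, errs on the safe side and does not affect this point.

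**2. What the coefficients mean.** Write the stated model as t2 = a + b·t0 + g′x + e, where x holds the covariates. The mean change is then

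E(t2) − E(t0) = a + (b − 1)·E(t0) + g′E(x).

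It combines several parameters with the baseline and covariate means. No single coefficient equals it.
- b is the association between the two scores.
- a is the expected t2 score when t0 is 0 and the covariates are at zero or reference.
- g describes the patient characteristics.

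**3. Size of the slope test.** Ignoring covariates and clustering, t = r√(n − 2)/√(1 − r²). With r = 0.5 and 10% drop-out:
- Phase 2: n = 280 × 0.9 = 252, and t = 0.577 × √250 = 9.1.
- Phase 3: n = 1,960 × 0.9 = 1,764, and t = 0.577 × √1,762 = 24.2.

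The mean change does not appear in the formula.

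**4. Simulation check.** The setting was 7 centres of 36 completers, r = 0.5, ICC 0.01 and 2,000 runs per scenario. The baseline mean of 70, SD of 20 and covariate distributions are assumptions.

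| True change | t0 slope, mean | Slope significant | Intercept, mean | Centre-level test of mean change significant |
|---|---|---|---|---|
| −0.3 SD | 0.50 | 100% | 28.7 | 92% |
| 0 | 0.50 | 100% | 34.7 | 4.8% |
| +0.3 SD | 0.50 | 100% | 41.1 | 92% |

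The slope is the same in all three scenarios. The intercept shifts with the change, but the value that means no change is about 35 here (70 − 0.5 × 70), not the 0 against which software tests it. The covariate terms were significant in about 5% of runs throughout. A second simulation (baseline mean 75, independent centre effects at t0 and t2, 3,000 runs per scenario) gave 5% at zero change and 85–86% at ±0.3 SD for the centre-level test.

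**5. A tempting repair that fails.** One could regress the change on t0 centred at its sample mean and test the intercept. The intercept then equals the mean change. Its model-based standard error, however, uses the residual variance (1 − r²)SD² = 0.75 SD², whereas the change has variance 2(1 − r)SD² = 1.00 SD². The ratio of standard errors is √0.75 = 0.866, about 13% too small. The true two-sided error at nominal 5% is 2[1 − Φ(1.96 × 0.866)] = 2[1 − Φ(1.697)] ≈ 9.0%. Simulation without clustering gave 9.3%, against 5.2% for a paired t test.

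**The case against.** Three arguments on the other side carry weight.

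*The section never says that the slope or intercept is the primary test.* This is true. A reader might infer that a significant primary result is practically guaranteed whatever happens to patients. The protocol does not support that, because it names differences between observations as the target and does not say which parameter will be tested.

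*The mean change can be obtained from the same fit.* This is also true. Regressing t2 on t0 and regressing the change on t0 are the same model with the slope shifted by 1, and the predicted t2 at mean covariates minus mean t0 is the mean change. Means with SDs are to be reported as well. It would therefore be too strong to say that the study can yield no estimate of change. What is missing is a stated contrast with a matching interval and test, and step 5 of the working shows that an obvious way of adding one is miscalibrated.

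*A journal article condenses, and an analysis plan may say more.* This would excuse silence on the model. Here, however, outcome, predictor, covariates and significance rule are all given, and together they miss the stated target.

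A reader might also infer that every other quantitative outcome is affected. Table 1 rules out a literal reading: the social support scale is collected only at t0, and the pathway-experience and shared-decision questionnaires only at t1. The mismatch passes to outcomes measured at both t0 and t2.

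An intercept that is almost always significant should not be used as evidence either. That depends on an assumed baseline mean, SD and covariate coding, which the protocol does not give.

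**Conclusion.** The point stands as a mismatch between the stated primary model and the stated target. The study is single-arm and sized on a t0-to-t2 change of 0.3, yet no parameter of the model estimates or tests that change. The algebra needs no numerical assumption. The slope statistics of about 9 and 24 use only the protocol's correlation, sample sizes and drop-out. The simulated rejection rates also depend on the assumed baseline distribution and on how the centre effect enters. The matter should be settled before analysis, because it concerns the primary outcome and leaves the choice of contrast open.

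**What to change.** Replace the model sentence in Data analysis with a long-format linear mixed model for physical functioning at t0 and t2. It should have a fixed time effect, a random patient effect, random centre and centre-by-time effects, and adjustment for age, gender and education. Name the time coefficient, with its 95% confidence interval and test against 0, as the primary result.

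An acceptable alternative takes t2 minus t0 as the outcome, with a random centre intercept and centred age, gender and education, and tests the intercept against 0. The t0 score must then stay out of the covariates, for the reason in step 5 of the working.

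Apply the scheme to secondary outcomes measured at both t0 and t2, and say that measures collected once are described only.

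The cost is one rewritten paragraph, with the same data and software. The planned multiple imputation and complete-case sensitivity analysis can stay. The change gives no reason to raise the sample size: 252 completers with a design effect of 1.39 are worth 252/1.39 ≈ 181 independent patients, about 98% power by formula for dz = 0.3. The simulated centre-level tests with seven centres gave 85–92%, above the planned 80%.

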### Participants and recruitment

Eligible for participation are cancer patients, at least 18 years old, with all cancer types regardless of the stage of the disease and during acute treatment. They show symptoms related to the disease or the treatment which have been shown to be positively impacted by exercise therapy (i.e. fatigue, emotional strain, polyneuropathy, reduced physical functioning, reduced quality of life) and/or they are interested in exercise therapy. Patients are included at all stages of their cancer treatment.

Patients are recruited for the study at the start or during the delivery of cancer treatment (medication, radiation, surgery, or combinations of these). They are approached by EOGs or referred by physicians or other specialists, patients may also approach EOGs or EOSs independently. Patients are informed about the study and the MOVE-ONKO care pathway. If they consent to participate in the study, they are asked to fill in the first survey and are enrolled in the MOVE-ONKO care pathway. Participation in the MOVE-ONKO care pathway involves participating in the study. There are no further incentives for the patients.

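### Multiple imputation and the complete-case check share one blind spot, drop-out that depends on the unseen 12-week score, so a tipping-point analysis should be added

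*Protocol article*

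**What the plan says.** All references are to the protocol article.

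- **Missing data (Data analysis).** The rule and the one check named are: "Missing values will be replaced by multiple imputation. An additional sensitivity analysis will only use complete cases". No exception to the imputation is given, and no analysis allowing for drop-out related to the unseen outcome is named.
- **Primary model (Data analysis).** Physical functioning is analysed "using a linear model with the value of physical functioning at t2 as dependent variable and its value at t0 as independent variable", with adjustment for centre, age, gender and education. The other quantitative outcomes follow the same scheme.
- **Population (Participants and recruitment, intervention outcomes).** Adults "with all cancer types regardless of the stage of the disease and during acute treatment".
- **Design (Study design; Evaluation of intervention outcomes).** Prospective, with no control group.
- **Planning values (Sample size calculation, intervention outcomes).** An effect size of 0.3 between t0 and t2, with "power = 0.80, intra-subject correlation = 0.5, intraclass correlation (ICC) = 0.01 (patients in centres), and drop-out = 10" (the last figure is a percentage); 280 patients in seven centres in phase 2 and about 1,960 in 56 centres in phase 3.
- **Timing (Table 1).** The full QLQ-C30 is collected at t0 and t2. EORTC item bank items are also collected at t3. Neither is collected at t1.

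**The concern.** A sensitivity analysis is useful if it rests on a different assumption from the primary analysis. Standard multiple imputation assumes that, given the observed data, patients who do not return the t2 questionnaire would have scored like those who do. In a regression of t2 on t0 and covariates, complete cases rest on essentially the same assumption. If patients stop answering because they have become less able, both analyses miss it, and their agreement may be read as reassurance.

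Two features of the study make this matter. Patients of any stage are followed through acute treatment, so functional decline by 12 weeks is a plausible reason for non-return. And there is no second arm in which a shift could cancel: whatever selective loss adds goes straight into the before-after change. At phase 3 size, even a small shift is large relative to the standard error.

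**Working it through.** **1. Do the two stated analyses differ?**
If t0 and the covariates are complete and only t2 is missing, imputation from the same covariates draws the missing scores around the regression line fitted to the completers. Refitting the model to the filled-in data returns that line apart from simulation noise. A simulation of the stated model confirms it (1,960 patients, within-patient correlation 0.5, true change 0, imputation from t0, change read at the baseline mean, clustering and other covariates left out):

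| Drop-out depends on | Share missing | Complete cases | Imputation |
|---|---|---|---|
| t0 score | 10 / 20 / 30% | 0.00 / 0.00 / 0.00 | 0.00 / 0.00 / 0.00 |
| worsening from t0 to t2 (odds of missing multiplied by e per SD) | 10 / 20 / 30% | +0.07 / +0.13 / +0.20 | +0.07 / +0.13 / +0.20 |

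The two agree when they are right and agree when they are wrong. Only the 10% is a document figure; 20% and 30% are assumptions that show the range.

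**2. Size of the shift at the planned drop-out**
Let f be the share missing and δ the amount by which drop-outs' change falls short of what the imputation predicts. The full-cohort mean is then the estimate minus f × δ, so

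bias = f × δ.

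- f = 0.10, δ = 0.5 SD: 0.10 × 0.5 = 0.05 SD
- f = 0.10, δ = 1.0 SD: 0.10 × 1.0 = 0.10 SD

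The δ values are assumptions; the article gives no figure.

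**3. Standard error of the mean change**
With correlation 0.5, the SD of change is √(2 × (1 − 0.5)) = 1 SD of the score. Equal centre sizes are assumed, and the design effect is 1 + (m − 1) × 0.01 with m completers per centre.

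- Phase 3: 1,960 × 0.9 = 1,764 completers; m = 1,764 / 56 = 31.5; design effect 1 + 30.5 × 0.01 = 1.305; SE = √(1.305 / 1,764) = 0.027. Smallest significant change (two-sided 5%, assumed): 1.96 × 0.0272 = 0.053 SD.
- Phase 2: 280 × 0.9 = 252 completers; m = 36; design effect 1.35; SE = √(1.35 / 252) = 0.073. Smallest significant change: 0.143 SD.

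**4. If the true change is zero**
The chance of a significant result is about Φ(bias / SE − 1.96).

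| | δ = 0.5 SD | δ = 1.0 SD |
|---|---|---|
| Phase 3, 10% missing | Φ(1.84 − 1.96) ≈ 45% | Φ(3.68 − 1.96) ≈ 96% |
| Phase 2, 10% missing | about 10% | about 28% |

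These are normal approximations for a test of mean change against zero; they do not reproduce the full planned model. The phase 2 figures include the small lower tail.

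**5. If the estimate is 0.3**
Correcting for δ = 0.5 leaves 0.30 − 0.05 = 0.25; for δ = 1.0, 0.20. Significance is lost at δ = (0.30 − 0.143) / 0.10 ≈ 1.6 SD in phase 2 and (0.30 − 0.053) / 0.10 ≈ 2.5 SD in phase 3. The effect reaches zero at 0.30 / 0.10 = 3 SD.

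**The case against.** The strongest reply is that this is a condensed article. The full protocol and analysis plan are not shown, and the imputation model, the treatment of deaths and further sensitivity analyses are matters an article commonly leaves to them. That stands for anything the article is merely silent on, including which variables enter the imputation. It does not remove the point about what the article does state: the check it names is poorly matched to the risk in this design.

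Three stronger readings are tempting, and the article does not support them.

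- **That the plan fills in scores for patients who have died.** The article does not mention death. The imputation sentence has no exception, but it does not say that a score after death counts as a missing value. This is inferred from silence.
- **That the complete-case analysis checks nothing.** If raw mean changes are compared and drop-out depends on t0, complete cases move (−0.05 SD at 10% missing, −0.13 at 30%) while imputation stays at 0.00, so that kind of loss would show. Missing covariates, or other t1 or t3 measures used in the imputation, could also separate the two analyses. The near-identity holds for the stated model when mainly t2 is missing and imputation uses the model's own covariates. Since the physical functioning scale is not collected at t1, other variables can narrow the blind spot but are unlikely to close it.
- **That worsening patients will inflate the result.** Decline that the observed data predict is dealt with by imputation. Inflation needs drop-outs to be worse than predicted, and the article gives no reasons for drop-out from which to judge this.

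**Conclusion.** The point holds as a limited one. Under the stated model, imputation and complete cases give practically the same answer and share the same exposure to drop-out that depends on the unseen t2 score. At the planned 10% drop-out, a shortfall of 0.5 to 1.0 SD would inflate the change by 0.05 to 0.10 SD. That would not overturn a true effect of 0.3 in either phase. It could make a null or small change significant in phase 3, where anything above about 0.053 SD is significant.

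The result rests on assumed shortfalls, equal centre sizes, a two-sided 5% test, and reading the primary result as the mean change at average baseline. Larger losses would make it more serious, but the article gives no figure above 10%. This is a cheap improvement to the stated check, not an error that invalidates the analysis.

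**What to change.** Keep the complete-case analysis and add a delta-adjusted (tipping-point) analysis: lower the imputed t2 scores in steps, for example from 0.1 to 1.0 SD, refit the primary model at each step, and report where the conclusion changes or that it does not change within the range.

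Also state that physical functioning is not imputed after death, report deaths by t2 separately, and define the primary estimate for patients alive at t2. If the full protocol or analysis plan already contains these rules, a cross-reference is enough.

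The cost is a few sentences, modest programming, and vital status or reason for non-return at t2 taken from centre files. Recruitment, questionnaires and visit timing do not change. The change should be fixed before the t2 data are analysed.

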#### Patient and public involvement

Patient involvement is a central part in the MOVE-ONKO studies. Besides a scientific and healthcare/insurance company counselling board, a counselling patient board meets every six months during the project time discussing relevant project development steps. Furthermore, representatives of all boards are involved in the curricula development of EOGs and EOSs and APP development.

## Discussion

If the implementation and evaluation of the MOVE-ONKO care pathway is successful, the aim is to transfer the pathway into standard care. In doing so, the MOVE-ONKO care pathway will address key barriers to the implementation of exercise therapy [42, 43].

Firstly, oncology patients will be comprehensively informed about the benefits and opportunities of exercise therapy and physical activity [1]. After comprehensive exercise counselling, they will be referred to needs-based exercise therapy programmes close to their home or they will be able to participate in online exercise therapy programmes.

Research has shown that exercise therapy advice combined with behavioural change techniques, delivered by healthcare providers, can improve patients' physical activity behaviour [44]. Furthermore, supervised exercise therapy shows greater effectiveness in terms of cancer- and cancer-related side effects than non-supervised programmes (e.g. home-based) [45]. However, MOVE-ONKO considers each patient's individual interest and personal barriers to exercise therapy, therefore home-based and online exercise therapy programmes are also available.

Secondly, the educational training of EOGs and EOSs will provide the necessary knowledge and technical support for healthcare providers to regularly advise exercise therapy to their cancer patients. In addition, comprehensive risk stratification allows for the referral of complex patients (e.g., those with severe symptoms or co-morbidities) to EOSs, reducing the complexity of the counselling service for EOGs [46].

Thirdly, we expect the development of regional exercise-based networks and multidisciplinary teamwork in the CCCs and remote cancer centres [47]. It will be of great interest to know which patients will be consulted by EOSs and which patients are transferred from EOGs to EOSs (e.g. due to high complexity or other issues). We expect different barriers and facilitators for CCCs due to different regional conditions and characteristics [18]. Overall, we predict an increase of the utilization of exercise therapy by patients through the involvement of multiprofessional healthcare providers in the MOVE-ONKO care pathway.

As there is currently no structured care pathway for exercise therapy in paediatric oncology, it is further planned to extend and adapt the MOVE-ONKO care pathway to paediatric cancer patients.

As independent cohorts of healthcare providers will be surveyed and interviewed, no within-person comparisons can be made. Key informant recruitment of healthcare providers may lead to social desirability bias. Outreach in phase 3 is hypothetical and it remains uncertain whether each CCC will reach an additional 7 remote cancer centres.

In the final phase of the study, the results will be published as a report. The results will be made available to the scientific community in the form of scientific publications and conference papers. Aggregated results of each CCCs implementation success will be made available to participating centres on request.

